### Study Preparation

#### Training of RA Nurses

Five RA nurses were recruited from NINS&H and another tertiary hospital, and 5 student nurses were recruited from 2 nursing schools for this study. Investigators provided protocol-specific theoretical and practical training to all RA nurses before the study initiation. They received training on physical measurements and were taught the motivational interviewing technique [36] to effectively encourage patients who had a stroke to adhere to instructions. We trained them how to educate patients to maintain daily activities and to send SMS text messages. Throughout the study, the RA nurses have been receiving monthly feedback sessions on the participants’ health education materials.

#### Data Monitoring and Quality Assurance

The investigators (medical doctors) are directly involved in patient management. The investigators and the RA nurses have regular biweekly meetings for study purpose. Pretesting of the questionnaires was done among the patients (5% of the sample of 432) who did not participate in the main study. Additionally, for regular quality control purpose, investigators independently check 5% of the study participants’ data on the same day by using field testing. The investigators check the process of taking consent, data collection, and physical examination by the RA nurses. The detected errors are corrected immediately at the field site. For any query, RA nurses consult with the investigators. RA nurses fill up the questionnaires and enter the data into a password-protected computer. Investigators check the data and resolve the queries.

### Ethics Approval

This study was approved by the institutional review board and the ethics review board of the NINS&H (IRB/NINSH/2022/151). All participants were explicitly informed about the study goals, significance, risks, and benefits, and their rights to participate in the study prior to the requirement. To participate in this study was entirely voluntary, and participants can withdraw at any point from their participation.

### Statistical Analysis

To compare the outcomes of the intervention group and the control group, we will conduct an intention-to-treat analysis and a full set analysis. A chi-square test will be performed for categorical data, and a 2-sided *t* test or Mann-Whitney *U* test will be employed for continuous variables, as appropriate, to compare the 2 groups. For the primary end point, the cumulative risk of recurrence and adverse events occurring in 12 months will be estimated using the Kaplan-Meier method and presented overall by age group and by stroke subtypes. For the secondary end points, an analysis of covariance will be conducted to assess the effect of the intervention on the outcomes by adjusting confounding variables. Changes in outcomes over time will be analyzed using repeated-measures analysis of variance as well as regression analysis. Friedman test will be performed to examine the changes within the groups. Associations between risk factors and outcomes will be tested using Cox proportional hazards models, adjusting for all baseline factors. Additionally, laboratory test and physical examination data will be analyzed using 2-sided *t* tests or 2-way repeated-measures analysis of variance, considering data normality. For the knowledge-related questionnaire, medication adherence–related questionnaire, and QoL, reliability checking will be performed, and total scores will be calculated. The significance level will be set at .05. Data analysis will be conducted using SPSS (version 26.0; IBM Corp).

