### Study Objectives

The objective of this study is to evaluate the effectiveness of a health education program for patients who had their first stroke (transient ischemic attack, hemorrhagic stroke, lacunar stroke, atherothrombotic stroke, or cardioembolic stroke) and their family caregivers in order to reduce the recurrence of stroke.

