### Randomization Schedule

A randomization schedule was used following the stratified randomization technique on a computer-generated series of numbers. On the basis of studies conducted in China [32,33], we stratified the patients into <65 years group and ≥65 years group, as the study site had no statistics about the age of the patients with recurrent stroke and types of strokes (hemorrhagic stroke, large artery atherosclerosis, cardioembolic, small vessel occlusion, lacunar, transient ischemic attack) because recurrence rates differed by the stroke type [6]. An experienced investigator who was not involved in this study generated the random allocation number by sequences. She distributed them in sealed opaque envelopes with serial numbers, which were kept in locked file cabinets in the hospital.

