#### Sample Size

Stroke recurrence rate in Bangladesh was 20% within 1 year in 2019 [8]. A study that evaluated the effectiveness of health education in preventing the recurrence of stroke showed 50% reduction among the intervention group compared to the control group [13]. The expected proportion of outcomes from the intervention group was assumed as P1=0.10; P2 (proportion of outcome from control group)=0.20; α=.05 (2-tailed), 1-β=.80; Z1-α/2=Z, α=1.96; and Z1-β=Z, β=.84. We found that the estimated sample size was 196 for each arm (a total 392 for both arms). By considering 10% dropout, the total sample size was 432 (216 for each arm).

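### Randomisation is stratified by age group and stroke type, but no planned between-arm test of 12-month recurrence uses those factors or follow-up time; the cost is small and the remedy is wording only

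*Protocol article*

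**What the plan says.** Under Randomization Schedule: "A randomization schedule was used following the stratified randomization technique on a computer-generated series of numbers". The factors are age (<65, >=65) and stroke type, the latter "because recurrence rates differed by the stroke type". Six types are listed there, including both small vessel occlusion and lacunar. Study Objectives has five: "transient ischemic attack, hemorrhagic stroke, lacunar stroke, atherothrombotic stroke, or cardioembolic stroke".

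The primary end point is the stroke recurrence rate at 12 months. Under Statistical Analysis, the methods are assigned as follows:

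- Comparison of the two groups: "A chi-square test will be performed for categorical data", and a t test or Mann-Whitney test for continuous variables. No strata or covariates are named.
- Primary end point: Kaplan-Meier, used to estimate 12-month cumulative risk and to show it overall, by age group and by stroke subtype. No between-arm test is attached.
- Secondary end points: analysis of covariance for the intervention effect, adjusted for confounders.
- Cox models adjusting for all baseline factors: associations between risk factors and outcomes.
- Analysis sets: "we will conduct an intention-to-treat analysis and a full set analysis". Neither is said to be decisive.

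**The concern.** The protocol calls stroke type prognostic and balances the arms on it, yet uses it only to display recurrence curves. An analysis that leaves out prognostic stratification factors carries a standard error that is too large for the balance achieved, so some of the benefit of stratifying is lost. Adjusted intervention effects are planned for the secondary end points but not for the primary one.

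There is also a mismatch between test and estimate. Kaplan-Meier uses the partial follow-up of patients who leave. In its simple form, a chi-square test on a 12-month proportion either excludes those patients or counts them as event-free. The plan expects 10% dropout, so the reported risk and the p value could rest on different data. In an open-label trial where one arm has more contact than the other, dropout may differ by arm, and the way dropouts are counted would then affect the result.

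**Working it through.** **1. The plan's own figure.** Inputs from Sample Size: "The expected proportion of outcomes from the intervention group was assumed as P1=0.10"; "P2 (proportion of outcome from control group)=0.20"; "α=.05 (2-tailed), 1-β=.80"; z values 1.96 and 0.84.

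n per arm = (1.96 + 0.84)² × (0.10×0.90 + 0.20×0.80) / (0.20 − 0.10)² = 7.84 × 0.25 / 0.01 = 196.

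With the 10% allowance, 196 × 1.10 = 215.6, so 216 per arm and 432 in all. The stated figures reproduce. The formula compares two proportions and uses neither strata nor follow-up time.

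**2. Why leaving out the strata is conservative.** Stratified allocation removes the between-stratum part of the outcome variance from the difference between arms, but the chi-square test still counts it. If that part is a share s of the variance, the test statistic under the null has standard deviation √(1 − s), and the true type I error is 2 × [1 − Φ(1.96/√(1 − s))]. This cannot exceed 0.05.

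**3. Size by simulation.** The documents give no recurrence rates by stratum, so these are assumptions:

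- 12 strata (2 age groups × 6 types), an age split of 60/40, and type shares of 10% to 25%.
- Overall control rate 20% and intervention rate 10%.
- 432 patients with 1:1 allocation within strata, and 40,000 trials per scenario.

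The comparator is the Cochran-Mantel-Haenszel (CMH) test over the same strata.

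| Assumed control rates across strata | s | Type I from the formula in step 2 | Type I, chi-square | Type I, CMH | Power, chi-square | Power, CMH |
|---|---|---|---|---|---|---|
| 20% everywhere | 0 | 0.050 | 0.051 | 0.051 | 0.837 | 0.836 |
| 11% to 34% (modest) | 0.0275 | 0.047 | 0.049 | 0.051 | 0.840 | 0.844 |
| 7% to 46% (strong) | 0.073 | 0.042 | 0.042 | 0.050 | 0.848 | 0.861 |
| 3% to 62% (extreme) | 0.1623 | 0.032 | 0.033 | 0.050 | 0.854 | 0.886 |

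The simulation error on a type I rate near 0.05 is √(0.05 × 0.95 / 40,000) = 0.001. The power lost is 0.844 − 0.840 = 0.4 points, 0.861 − 0.848 = 1.3 points, and 0.886 − 0.854 = 3.2 points.

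**4. Size of the censoring issue.** Assumptions: 216 per arm, constant hazards giving 20% and 10% at 12 months, dropout times uniform over the year, and 15,000 trials per scenario. Chi-square results are given with dropouts counted as event-free / with event-free dropouts excluded.

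| Dropout, intervention v control | Type I, chi-square | Type I, log-rank | Power, chi-square | Power, log-rank |
|---|---|---|---|---|
| 10% v 10% | 0.051 / 0.050 | 0.049 | 0.825 / 0.825 | 0.828 |
| 5% v 15% | 0.058 / 0.060 | 0.052 | 0.761 / 0.872 | 0.822 |
| 15% v 5% | 0.059 / 0.059 | 0.051 | 0.864 / 0.748 | 0.817 |

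The simulation error on a type I rate is √(0.05 × 0.95 / 15,000) = 0.002. With equal dropout the tests agree. With a 10-point difference between arms, type I error is about 0.06, and power ranges from 0.75 to 0.87 according to how dropouts are counted.

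**5. Events per stratum.** At the planned rates, 196 × 0.10 + 196 × 0.20 = 58.8 events are expected among 392. Over 12 strata that is 58.8 / 12 = 4.9 each on average, so some strata will be sparse.

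**The case against.** The strongest reply is that this is a condensed article. It gives the primary end point a sentence of its own, naming Kaplan-Meier, and it plans Cox models that adjust for all baseline factors. The test that accompanies Kaplan-Meier is commonly left to the analysis plan. The loss is small, and in every scenario of step 3 the chi-square test has more than the planned 80% power. Both arms are telephoned at least monthly for a year, which should limit unknown outcomes, and the protocol gives one dropout figure that is not split by arm.

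Much of this stands, and it rules out three stronger readings that a reader might infer:

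- *The chi-square test is the declared primary test.* The text assigns it to categorical data in general. That it would decide the trial is an inference, supported by the two-proportion sample size and by the lack of any other fitting test.
- *The plan ignores censoring.* Kaplan-Meier is specified. The gap is that neither it nor the Cox model is given the job of testing intervention against control.
- *The false-positive rate is inflated.* Leaving out the strata lowers it. A rise appears only through unequal dropout, which the documents do not predict.

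What does not stand is that the point is only missing detail. The section gives each method a job, and those jobs leave both stratification factors out of the comparison of recurrence between arms.

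**Conclusion.** The point holds as a minor, cost-free improvement. The strata are fixed at randomisation and stroke type is called prognostic, yet no stated between-arm test of recurrence uses them or follow-up time. Leaving out the strata gives a slightly conservative test with a small loss of power. The censoring part matters only if dropout differs between arms.

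The sizes rest on assumed stratum shares, stratum rates, dropout patterns and constant hazards. The Background cites 14.7% recurrence at 3 months against 20% at 1 year. If events come that early, fewer would be missed by counting later dropouts as event-free.

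A reader might also infer from the objectives that the analysis should use five stroke types. The documents do not support that: the randomisation list has six, and the analysis should follow the strata actually used to allocate patients.

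**What to change.** Before the data are analysed, name one primary between-arm analysis: intention-to-treat, time to recurrence over 12 months, with dropouts censored at last contact. Use either a log-rank test stratified by age group and stroke type, or a Cox model with arm, age group and stroke type. State which of the two is primary, and give the full set analysis a supporting role.

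Take the strata as they were used at randomisation, say whether small vessel occlusion and lacunar were separate there, and prespecify how sparse stroke types are pooled, given about 59 expected events. Keep the chi-square test as a sensitivity analysis, with a stated rule for counting dropouts.

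The cost is analysis wording. Both factors were recorded at randomisation, no new data are needed, and the sample size stays at 432.

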**Methods:**

This is a parallel, open-label, prospective randomized controlled trial conducted at the National Institute of Neurosciences & Hospital in Dhaka, Bangladesh. We enrolled ≥18-year-old patients of both sexes who had a history of first stroke attack (transient ischemic attack, hemorrhagic stroke, lacunar stroke, atherothrombotic stroke, or cardioembolic stroke). We stratified patients into those aged <65 years and those aged ≥65 years and according to types of strokes for randomization. Our estimated sample size was 432. The intervention group receives face-to-face counseling on lifestyle modifications, blood pressure monitoring, and medication compliance–related health education during enrollment and monthly follow-ups. However, the control group receives only usual care from the hospital. The primary end point of this study is the reduction in the stroke recurrence rates at the end of the 12-month follow-up period. The secondary end points are to (1) assess the occurrence of all adverse events such as other cardiac events and all-cause mortality, (2) evaluate the status of the controlling modifiable risk factors such as blood pressure, glycated hemoglobin, and non–high-density lipoprotein cholesterol, (3) assess the knowledge related to stroke by using the investigator-developed questionnaire, (4) evaluate the lifestyle behavior related to stroke by using the investigator-developed questionnaire, (5) assess medication adherence, and (6) evaluate the quality of life of patients who had a stroke and their family caregivers. The evaluation points will be at baseline, 6 months, and 12 months for both groups.

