### Outcomes and Data Collection Procedure

#### Primary Outcome

The primary end point is the recurrence rate of stroke at 12 months.

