### Operational Definitions for This Study

#### Recurrence of Stroke

Recurrent stroke is defined as a new stroke event occurring at least 28 days after the stroke incident [32], which is confirmed by the physician who treats and diagnoses the patients in this study.

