#### Adverse Events

All adverse events (all causes of death, cardiovascular events) refer to all cases that need to be diagnosed, for example, recurrence of stroke, new onset of acute myocardial infarction and unstable angina, heart failure with hospitalization, and peripheral arterial disease with hospitalization—those that are confirmed by the physician who treats and diagnoses the patients in this study.

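### Kaplan-Meier is named as the estimator of 12-month stroke recurrence although death without recurrence is a recorded competing event, so the absolute recurrence risks will be overstated

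*Protocol article*

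**What the plan says.** Under Primary Outcome the protocol article states: "The primary end point is the recurrence rate of stroke at 12 months". The operational definition reads: "Recurrent stroke is defined as a new stroke event occurring at least 28 days after the stroke incident". Death is not a component of either.

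Death is nevertheless collected. The abstract lists a secondary aim to "assess the occurrence of all adverse events such as other cardiac events and all-cause mortality", and the operational definition of adverse events begins: "All adverse events (all causes of death, cardiovascular events) refer to all cases that need to be diagnosed". That definition goes on to include recurrent stroke itself.

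Statistical Analysis then says, for the primary end point, that "the cumulative risk of recurrence and adverse events occurring in 12 months will be estimated using the Kaplan-Meier method". The results are to be shown overall, by age group and by stroke subtype. The same section states that "A chi-square test will be performed for categorical data", and describes the time-to-event regression thus: "Associations between risk factors and outcomes will be tested using Cox proportional hazards models, adjusting for all baseline factors". The article does not mention competing risks or a cumulative incidence function, and does not say how a death enters the recurrence estimate.

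**The concern.** The quantity is called a cumulative risk over 12 months, that is, the share of patients who have a recurrence within a year. Kaplan-Meier for recurrence alone treats a patient who died without recurrence as censored, as if that patient could still have a recurrence at the rate of those still under observation. The result describes a hypothetical setting in which nobody dies first, not the risk named in the end point.

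Deaths are plausible. Patients have no upper age limit, hemorrhagic stroke is eligible, and modified Rankin scores up to 4 are accepted. Curves are planned by age group and stroke subtype. If those strata differ in mortality, their recurrence risks are overstated by different amounts, and the comparison between strata is distorted.

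The same sentence also puts adverse events under the primary end point, although the abstract and the Secondary Outcomes section list them as secondary. Since that outcome contains both death and recurrence, a reader cannot tell from the sentence which curve is the primary result.

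**Working it through.** **The plan's own figures.** From Sample Size: control 0.20 ("Stroke recurrence rate in Bangladesh was 20% within 1 year in 2019"), intervention 0.10, two-sided alpha 0.05, power 0.80.

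- Per arm: (1.96 + 0.84)² × (0.10 × 0.90 + 0.20 × 0.80) / 0.10² = 7.84 × 0.25 / 0.01 = 196, as stated.
- With 10% added: 196 × 1.1 = 215.6, so 216 per arm and 432 in total, as stated.

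The calculation compares two proportions and does not use the Kaplan-Meier estimate.

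**Direction of the error.** Let λ1 be the hazard of recurrence and λ2 the hazard of death without recurrence. The cumulative incidence weights λ1 at each time by the probability of being alive and free of recurrence. 1-KM with deaths censored weights it by a survival function built from λ1 alone, which is never smaller. So 1-KM is at or above the cumulative incidence, whatever the shape of the hazards.

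**Size.** The article gives no 12-month mortality for this population, so the proportion dying without recurrence, d, is assumed and varied from 2% to 20%. With constant hazards and true 12-month recurrence c:

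- L = λ1 + λ2 = -ln(1 - c - d)
- λ1 = L × c / (c + d)
- 1-KM = 1 - exp(-λ1)

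Example with c = 0.20 and d = 0.10: L = -ln(0.70) = 0.357; λ1 = 0.357 × 0.20 / 0.30 = 0.238; 1-KM = 1 - exp(-0.238) = 0.212.

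| Deaths without recurrence (assumed, equal in both arms) | 1-KM if true risk is 20% | 1-KM if true risk is 10% | Difference, points (true 10) | Ratio (true 0.50) |
|---|---|---|---|---|
| 2% | 20.2% | 10.1% | 10.1 | 0.50 |
| 5% | 20.6% | 10.3% | 10.3 | 0.499 |
| 10% | 21.2% | 10.6% | 10.6 | 0.499 |
| 15% | 21.8% | 10.9% | 11.0 | 0.498 |
| 20% | 22.5% | 11.2% | 11.3 | 0.497 |

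(Differences and ratios are computed before rounding.) The excess is 0.2 to 2.5 points at a true 20% and 0.1 to 1.2 points at a true 10%, or about 1% to 13% in relative terms.

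**Does mortality alone move the Kaplan-Meier contrast?** In the example, λ1 = 0.238 and λ2 = 0.119. Halve λ2 to 0.0595 and leave λ1 alone:

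- 1-KM = 1 - exp(-λ1) does not contain λ2 and stays at 21.2%.
- Cumulative incidence = λ1/(λ1 + λ2) × (1 - exp(-(λ1 + λ2))) = 0.238/0.297 × (1 - exp(-0.297)) = 0.206, up from 0.200.

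So it is the cumulative incidence that responds to a change in mortality. This matters for what has to be reported beside it.

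**The case against.** The strongest case against the point is that the flaw is small and confined to description. Much of this stands.

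- **The between-group test need not carry the bias.** The end point is a rate at 12 months, powered as two proportions, and the chi-square test is the stated comparison for categorical data. A crude proportion keeps patients who died in the denominator. The Kaplan-Meier sentence speaks of estimating and presenting and names no test.
- **The size is assumed.** At 5% deaths the excess is 0.6 and 0.3 points. The standard error of a 20% risk with 216 patients is √(0.20 × 0.80 / 216) = 2.7 points, so even the excess at 20% deaths (2.5 points) lies within one standard error. The eligibility criteria exclude modified Rankin score 5, multiorgan failure and terminal illness, which lowers expected mortality. A fatal stroke that meets the recurrence definition is an event, not a competing death.
- **Deaths are not lost to the trial.** A reader might infer that they disappear as censored observations. They drop out only of the recurrence curve. They count in the adverse-event outcome, which the same sentence also estimates over 12 months.
- **A change in mortality does not by itself shift the Kaplan-Meier contrast.** A reader might infer that education which alters mortality would move it for reasons unrelated to recurrence. Under the model used here the reverse is true, as shown above. Holding the true risks at 20% and 10% with 20% control and 10% intervention deaths does bring the ratio to 0.47, but that scenario changes the recurrence hazards as well. Dependence between death and recurrence could move the contrast, but nothing in the article allows that to be sized.
- **Handling of deaths is often left to an analysis plan, and none is shown.** This does not remove the point, because the article itself fixes the estimator. Censoring at death is not stated, but it is what ordinary Kaplan-Meier for recurrence alone implies.

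**Conclusion.** The point holds for the absolute recurrence risks. Kaplan-Meier is the named estimator of a risk that excludes death, in a trial that records death, so the published 12-month recurrence figures will be too high if any patients die without recurrence before others have one. At the protocol's planning rates and an assumed 2% to 20% of deaths without recurrence, the excess is 0.2 to 2.5 points at a true 20% and 0.1 to 1.2 points at a true 10%. It is largest where mortality is highest, so the displays by age group and stroke subtype are the most exposed.

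These figures rest on constant hazards and on assumed mortality; only the direction follows from the method itself. With equal mortality the ratio stays near 0.50. The sample size and a chi-square test on crude proportions are untouched. The article does not support a claim that the treatment comparison as a whole is invalid.

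Separately, the placement of adverse events under the primary end point conflicts with the outcome lists and needs correction in any case.

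**What to change.** 1. Estimate recurrence by the cumulative incidence function (Aalen-Johansen) with death without recurrence as the competing event, by arm and in the planned age and subtype strata.
2. Report beside it the cause-specific hazard ratio for recurrence and all-cause death by arm. The cumulative incidence itself depends on mortality, so it should not be read alone.
3. Keep Kaplan-Meier for the composite that includes death.
4. Reword the sentence so that recurrence alone is primary and adverse events are secondary, as in the abstract and the two outcome sections.

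Cost: wording in the analysis plan and, if the named SPSS release does not offer the estimator, a short script in other software. All-cause death is already an outcome, so no new end point is needed, and the sample size does not change.

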### Study Procedure

Enrollment occurred over a span of 6 consecutive days during morning hours, excluding government holidays, within a week. After determining eligibility and obtaining consent, the RA nurses opened the sealed randomization envelope in the presence of the participants. They collected demographic information, conducted physical examinations, and filled up questionnaires (Table 1).

**Table 1 table1:** Study activities.

Schedule	Intervention group	Control group
At baseline	Data collection by RA^a^ nurses through structured questionnaires RA nurses provide knowledge-related health education before discharge or after the hospital visit: health education (face-to-face, 45 min) by RA nurse and exercise session by the physiotherapist RA nurses perform physical examination: BP^b^ level (systolic and diastolic) Blood tests: HbA_1c_^c^, total cholesterol, and HDL cholesterol (calculate non-HDL cholesterol)	Data collection by RA nurses through structured questionnaires Provide usual practice RA nurses perform physical examination: BP level (systolic and diastolic) Blood tests: HbA_1c_, total cholesterol, and HDL^d^-cholesterol (calculate non-HDL cholesterol)
Middle of study (6 months)	Data collection by RA nurses through structured questionnaires RA nurses provide refresher health education same as baseline RA nurses perform physical examination: BP level (systolic and diastolic) Blood tests: HbA_1c_, total cholesterol, and HDL cholesterol (calculate non-HDL cholesterol)	Data collection by RA nurses through structured questionnaires Provide usual practice RA nurses perform physical examination: BP level (systolic and diastolic) Blood tests: HbA_1c_, total cholesterol, and HDL cholesterol (calculate non-HDL cholesterol)
End of study (12 months)	Data will be collected by RA nurses through structured questionnaires RA nurses will perform physical examination: BP level (systolic and diastolic) Laboratory tests: HbA_1c_, total cholesterol, and HDL cholesterol (calculate non-HDL cholesterol)	Data will be collected by RA nurses through structured questionnaires RA nurses will provide health education at the end of the study, and a health education booklet will be given to them RA nurses will perform physical examination: BP value (systolic and diastolic) Laboratory tests: HbA_1c_, total cholesterol, and HDL cholesterol (calculate non-HDL cholesterol)

^a^RA: research assistant.

^b^BP: blood pressure.

^c^HbA_1c_: glycated hemoglobin.

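### Continuous secondary outcomes have overlapping analyses: the outcome's own baseline value is not named as a covariate, and repeated-measures ANOVA and Friedman tests use only patients with all three visits

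*Protocol article*

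**What the plan says.** The Statistical Analysis section promises an intention-to-treat and a full set analysis. For continuous outcomes it then names:

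- a two-sided t test or Mann-Whitney U test between the groups;
- for the secondary end points, ANCOVA: "an analysis of covariance will be conducted to assess the effect of the intervention on the outcomes by adjusting confounding variables";
- for change over time: "Changes in outcomes over time will be analyzed using repeated-measures analysis of variance as well as regression analysis";
- within each arm: "Friedman test will be performed to examine the changes within the groups";
- for laboratory and examination data, t tests or "2-way repeated-measures analysis of variance, considering data normality".

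The Abstract sets evaluations at baseline, 6 and 12 months. Table 1 (Study Procedure) schedules blood pressure, questionnaires and blood tests in both arms from baseline onwards: "Blood tests: HbA_1c_, total cholesterol, and HDL cholesterol (calculate non-HDL cholesterol"). The Intervention Group Study Plan says that if patient and caregiver cannot attend at 6 months, the nurses collect the data by telephone. The Sample Size section allows for 10% dropout.

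**The concern.** Blood pressure, HbA1c and non-HDL cholesterol fall under two rules: the ANCOVA for secondary end points, and the later sentence giving laboratory and examination data to t tests or repeated-measures ANOVA. The normality condition does not settle which of those last two applies, because both assume normal errors. The analysis that yields the reported effect could therefore be picked after the data are seen.

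The named methods also differ in how they use the data:

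- **Baseline.** A t test on 12-month values ignores the baseline measurement. A change-score t test or repeated-measures ANOVA uses it, but inefficiently. ANCOVA would use it well, but the text names only confounders, and randomisation already removes systematic confounding. The covariate that matters most for precision is the outcome's own baseline value.
- **Incomplete patients.** Classical repeated-measures ANOVA and Friedman tests drop anyone without all three values. A telephone call cannot supply HbA1c, cholesterol or a nurse-performed blood pressure reading.
- **Comparison.** A Friedman test within one arm does not compare the arms.

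At stake are precision, and the freedom to choose among results, on outcomes that carry the trial's account of how education works. The Conclusions section also ties introduction of the programme in the health care system to quality of life, one of these outcomes.

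**Working it through.** **1. The plan's own figure.** Inputs from Sample Size: "The expected proportion of outcomes from the intervention group was assumed as P1=0.10", "P2 (proportion of outcome from control group)=0.20", "α=.05 (2-tailed), 1-β=.80".

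n per arm = (1.96 + 0.84)² × (0.10×0.90 + 0.20×0.80) / 0.10² = 7.84 × 0.25 / 0.01 = 196. Then 392 × 1.10 = 431.2, rounded up to 432. The stated figures reproduce. They concern the primary end point only; no power is stated for the secondary outcomes.

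**2. Use of the baseline value.** The protocol gives no SD or correlation, so r between baseline and 12 months is assumed to be 0.3 to 0.7. The variance of the arm contrast, relative to a 12-month t test, is 2(1−r) for a change score (or the baseline-to-12-month contrast of repeated-measures ANOVA) and 1−r² for baseline-adjusted ANCOVA. The ratio of ANCOVA to change score is (1−r²)/[2(1−r)] = (1+r)/2.

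| r | 12-month t test | Change score | ANCOVA | ANCOVA / change score |
|---|---|---|---|---|
| 0.3 | 1 | 1.40 | 0.91 | 0.65 |
| 0.5 | 1 | 1.00 | 0.75 | 0.75 |
| 0.7 | 1 | 0.60 | 0.51 | 0.85 |

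**3. Patients kept, per arm of 216.** Missingness at 12 months is set at the planned 10%; at 6 months it is assumed to be 10% to 30%. Patients with a 12-month value: 216 × 0.90 = 194.4. Patients with all three values, if the two losses are independent: 216 × 0.90 × (1 − m6). If they overlap fully: 216 × (1 − the larger of the two).

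| Missing at 6 months (m6) | All three values, independent | All three values, full overlap | 12-month value present |
|---|---|---|---|
| 10% | 175.0 | 194.4 | 194.4 |
| 20% | 155.5 | 172.8 | 194.4 |
| 30% | 136.1 | 151.2 | 194.4 |

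**4. Both effects together.** At r = 0.5 and independent 10% losses, the change contrast on three-visit completers has (1.00/175.0) / (0.75/194.4) = 1.48 times the variance of ANCOVA on everyone with a 12-month value.

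**5. Simulated power.** Settings: 216 per arm, 3,000 replicates, effect 0.27 SD, equal correlation between visits, data missing completely at random, 10% missing at 12 months. The effect is what 216 per arm detects with 80% power by a t test: 2.80 × √(2/216) = 0.27. Ranges run over the three values of m6.

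| r | 12-month t test | ANCOVA, all 12-month values | Change contrast, three-visit completers (m6 = 10 / 20 / 30%) |
|---|---|---|---|
| 0.3 | 0.755–0.762 | 0.795–0.807 | 0.565 / 0.504 / 0.469 |
| 0.5 | 0.750–0.767 | 0.861–0.873 | 0.709 / 0.652 / 0.599 |
| 0.7 | 0.740–0.771 | 0.959–0.965 | 0.905 / 0.851 / 0.806 |

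Baseline-adjusted ANCOVA is the best of the three throughout.

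**The case against.** The strongest reply is that the plan already has the right method. It states that ANCOVA assesses the effect of the intervention, and gives repeated-measures ANOVA and Friedman the separate jobs of describing change over time and within groups. Covariate lists and missing-data rules commonly sit in an analysis plan, which is not shown. Much of this stands, and it rules out several stronger readings that a reader might infer:

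- *That every listed test drops anyone with a missed visit.* A single-visit t test or ANCOVA loses only patients without that visit's value.
- *That the plan contradicts its intention-to-treat promise.* The protocol does not state how missing values are handled, and imputation is not excluded. The tension comes from naming methods that in classical form need complete data.
- *That ANCOVA leaves the baseline value out.* The wording does not name it, but does not exclude it. Secondary Outcomes also defines most outcomes as changes, so baseline enters in that way.
- *That within-arm p values will be compared as evidence of effect.* Friedman is described only as a within-group test.
- *That 6-month visits by telephone are expected and questionnaire data will be lost.* The call is a contingency, and questionnaires can be completed by telephone. The gap concerns blood tests and nurse-measured blood pressure.

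The reply does not remove the separate sentence for laboratory and examination data. That sentence names t tests or repeated-measures ANOVA, not ANCOVA, for the outcomes most exposed to a missed hospital visit.

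**Conclusion.** The point holds as an avoidable loss of precision and an open choice of method, confined to secondary outcomes. It is not an error that invalidates the trial. The variance ratios are exact given r, but r is assumed. The loss of about 41 patients per arm (216 − 175), against about 22 for an analysis needing only the 12-month value (216 − 194), rests on an assumed 10% missing at 6 months, independent of 12-month loss. It disappears if the same patients miss both visits, and grows if more blood tests are missed at 6 months. Whether completers-only analysis would also bias the comparison depends on why visits are missed, which the protocol cannot tell us.

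**What to change.** For each continuous secondary outcome, laboratory and blood pressure data included, designate one between-arm analysis of the 12-month value, adjusted for the outcome's own baseline value and the two stratification factors, age group and stroke type, using all observed data. Either form would do:

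- a mixed model for repeated measures on the 6- and 12-month values, with arm, visit and their interaction, reporting the 12-month arm difference; or
- the ANCOVA already planned, with these covariates named.

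Remove the choice between t test and repeated-measures ANOVA on grounds of normality, and label the within-arm Friedman tests descriptive only. The cost is a few sentences in the analysis plan, settled before the outcome data are analysed. No new data are needed, and standard software fits both models.
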